**Methods:**

This is a multicenter, prospective, observational longitudinal cohort study. The primary outcome is the incidence of major adverse cardiovascular events (MACE) including in-stent restenosis, severe ventricular arrhythmia, heart failure, recurrent angina pectoris, and sudden cardiac death, and stroke one year later after ACS. Demographic characteristics, clinical data, treatments, and outcomes are collected by local investigators. Furthermore, freshly processed samples will be stained and assessed by flow cytometry. The expression of S100A4, CD47, SIRPα and Tim-3 on monocytes, macrophages and T cells in ACS patients were collected. Follow-up: during hospitalization, 3, 6 and 12 months after discharge.

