### Primary outcomes

Primary outcomes of this cohort are major adverse cardiovascular events within 1 year, including in-stent restenosis, severe ventricular arrhythmia, heart failure, recurrent angina pectoris, and sudden cardiac death.

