### Secondary outcomes

Secondary outcomes include the occurrence of these condition within 1 year: i)No reflow after PCI (after reperfusion treatment, blood flow of coronary artery is slowed down or completely absent); ii)Atrial fibrillation; iii) All-cause death except cardiovascular death; iv) Stroke/cerebrovascular accident.

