** LDL-C(≤ 1.4 mmol/L)**				
**Outcomes**				
In-stent restenosis				
Severe ventricular arrhythmia				
Heart failure				
Recurrent angina pectoris				
Sudden cardiac death				
No reflow				
Atrial fibrillation				
Death from other causes other than cardiac death				
Stroke/cerebrovascular accident				

Including daily living conditions (whether to follow a low-salt and low-fat diet, whether there is proper exercise, whether to quit smoking, drinking, etc.), and whether to use medications for secondary prevention for CHD, including antiplatelet agents, statins, angiotensin-converting enzyme inhibitor(ACEI)/angiotensin II receptor(ARB), β blocker, and whether the dose of ACEI/ARB and β blocker meets the recommended dose, blood pressure control(≤ 130/80 mmHg), blood glucose control(fasting blood glucose ≤ 6.0 mmol/L, 2 h postprandial blood glucose ≤ 11.0 mmol/L, or glycosylated hemoglobin ≤ 6.5%), control of low-density lipoprotein cholesterol(LDL-C) (≤ 1.4 mmol/L) and occurrence of MACE which including in-stent restenosis, severe ventricular arrhythmia, heart failure, recurrent angina pectoris, and sudden cardiac death. The content of follow-up also includes no reflow, atrial fibrillation, occurrence of death from other causes other than cardiac death, and stroke/cerebrovascular accident. The definition of all outcomes is presented in Table 2.

**Table 2 Tab2:** Definition of the outcomes

Events (during hospitalization or follow-up)	Definition
In-stent restenosis	In-stent restenosis is defined if it is observed during coronary angiography reexamination
Severe ventricular arrhythmia	Including ventricular tachycardia, ventricular fibrillation captured by ECG or ECG monitoring
Heart failure	The patients had typical symptoms of heart failure (such as chest tightness, dyspnea, etc.) combined with cardiac ultrasound suggesting decreased cardiac systolic or diastolic function or accompanied by elevated NT-proBNP
Recurrent angina pectoris	If symptoms that are similar or even aggravated to previous angina symptoms like location, time, and degree of pain still occur after PCI
Sudden cardiac death	Sudden cardiac death due to coronary heart disease
No reflow	No coronary reflow or slow flow is observed during PCI or coronary angiography reexamination
Atrial fibrillation	Paroxysmal or persistent atrial fibrillation captured by ECG or ECG monitoring

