Death from other causes other than cardiac death	Death from other causes other than cardiac death, such as stroke, cancer, etc
Stroke/cerebrovascular accident	Including ischemic stroke, hemorrhagic stroke diagnosed in hospital or through cerebral magnetic resonance imaging or diffusion weighted imaging report

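### Non-sudden cardiac death is in no death outcome, so such a patient counts as MACE-free unless a non-fatal component was recorded first, and the secondary death outcome is worded two ways

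*Protocol article*

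**What the plan says.** All references are to the protocol article.

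- **Primary outcomes.** MACE within one year, "including in-stent restenosis, severe ventricular arrhythmia, heart failure, recurrent angina pectoris, and sudden cardiac death". The last item is the only fatal one.
- **Secondary outcomes.** The third item is "All-cause death except cardiovascular death". Stroke is a separate fourth item: "iv) Stroke/cerebrovascular accident".
- **Table 2, fatal MACE component.** "Sudden cardiac death due to coronary heart disease". No time limit says what makes a death sudden.
- **Table 2, other deaths.** "Death from other causes other than cardiac death, such as stroke, cancer, etc".
- **Abstract, Methods.** Here stroke is part of the primary outcome: "recurrent angina pectoris, and sudden cardiac death, and stroke one year later after ACS".
- **Follow-up.** This section says that Table 2 defines all the outcomes. Neither Table 1 nor Table 2 has a row for a cardiac death that is not sudden, or for a recurrent infarction.
- **Statistical analysis.** Predictors of the outcome are selected by stepwise logistic regression and then taken into ROC analysis. Both need a yes/no MACE status for each patient. No rule is given for a death outside the listed outcomes.

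**The concern.** The two death outcomes should between them cover every death, and they do not. A patient who dies in hospital of progressive pump failure, or some days after a second infarction, has died a cardiac death that may not be sudden. The primary list does not hold that death, and the secondary outcome excludes it under either wording. Taken literally, the definitions put such a patient in the same group as an event-free survivor unless some other component had already been recorded.

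This bears on the study's question. The Background ties dysregulated inflammation to adverse remodelling and MACE, and the Discussion ties it to heart failure. If the immune markers relate to these deaths in the same direction as to the other components, placing the deaths among the non-events weakens the associations and the ROC results that the study is meant to produce. With few events expected, a handful of misplaced patients is not negligible.

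The second issue is narrower. The secondary death outcome excludes cardiovascular deaths in one place and only cardiac deaths in another, so the same death can be counted or not depending on which text the local investigator follows.

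**Working it through.** **Step 1. Assign each kind of death to the definitions.**

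| Death | Primary outcome (Methods, Table 2) | Secondary death outcome (Methods) | Secondary death outcome (Table 2) |
|---|---|---|---|
| Sudden cardiac, coronary cause | yes | no | no |
| Cardiac, not sudden | **no** | **no** | **no** |
| Stroke | no | no, if stroke is read as cardiovascular | yes, by name |
| Vascular, neither cardiac nor stroke | no | no | yes |
| Cancer or other non-cardiovascular | no | yes | yes |

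The second row is the gap. It exists under both wordings and needs no interpretation. The third and fourth rows show the mismatch between the two wordings. Under the abstract, the stroke itself would also make the patient a MACE case.

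**Step 2. Ask when a patient in the second row is still a MACE case.** Only when a non-fatal component was recorded before death. Heart failure is defined broadly; its Table 2 entry begins "The patients had typical symptoms of heart failure (such as chest tightness, dyspnea, etc.) combined with cardiac ultrasound" and also allows raised NT-proBNP. Many pump-failure deaths would therefore already be MACE. Ventricular arrhythmia on ECG or monitoring, and angina symptoms after PCI, would capture others. A fatal reinfarction is the clearer gap, because infarction is not a component. It is caught only if, for example, its pain was recorded as recurrent angina.

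**Step 3. Size.** No figure in the document rests on these definitions, so there is no planned figure to reproduce except the cited event rate.

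Inputs from Sample size: 151 of 1864 patients with MACE at one year, 150 to be enrolled, 10% loss to follow-up.

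- Rate: 151 / 1864 = 0.081, as stated.
- Expected MACE: 150 × 0.081 = 12.15 of those enrolled. With 10% lost, 150 × 0.90 = 135 and 135 × 0.081 = 10.9.

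Assumed, because the document gives neither: cardiac death within one year, *d* = 1–3%; share of those deaths that are non-sudden with no earlier component, *s* = 25–75%.

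Misclassified patients = N × *d* × *s*. The ratio to expected MACE is *d* × *s* / 0.081, which does not depend on N.

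| *d* | *s* | of 150 | of 135 | relative to expected MACE |
|---|---|---|---|---|
| 1% | 25% | 0.38 | 0.34 | 3.1% |
| 2% | 50% | 1.50 | 1.35 | 12.3% |
| 3% | 75% | 3.38 | 3.04 | 27.8% |

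The chance of at least one such patient among 150 is 1 − (1 − *ds*)^150. It runs from 0.31 in the first row to 0.97 in the last.

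**The case against.** The best defence has four parts.

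1. **The non-fatal components are broad.** Most cardiac deaths would be preceded by recorded heart failure, arrhythmia or angina. This stands, and it limits the size. A reader might infer that everyone who dies a non-sudden cardiac death is analysed as MACE-free; the documents do not support that. What remains is the patient with no recorded component before death.

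2. **Stroke death does not touch the primary outcome in the Methods.** This also stands. A reader might infer that fatal strokes are a further group of disease deaths hidden among the non-events. In fact the stroke is captured as a secondary outcome in its own right, and as MACE under the abstract. The conflict over stroke death also depends on reading stroke as cardiovascular, a term the document does not define, although the abstract's MACE list supports that reading. Since Table 2 is said to hold the definitions, the Methods item could be seen as a loose label. That makes it a wording mismatch, but one that should not remain.

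3. **Coding is inferred.** The article does not say how an unlisted death is coded, and an analysis plan that is not shown may deal with it. This stands in part: coding as a non-event is what the definitions imply, not something the text states. The definitions themselves are on the page, however, and they leave the gap.

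4. **The size is assumed.** This stands. A larger range results if all of an assumed 1–3% are taken to be non-sudden with no earlier component: 135 × 0.01 to 135 × 0.03 is 1.4 to 4.1 patients, or 12% to 37% of 10.9 events. That makes no allowance for components recorded first, so it is at most an upper bound. The 8.1% comes from a cited study whose MACE definition is not given; if this study's broader, partly symptom-based MACE is more frequent, the percentages fall. Bias toward no association is likewise conditional on the markers acting on these deaths in the same direction as on the other components, which no part of the document shows.

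**Conclusion.** The point holds. Non-sudden cardiac death is in no death outcome, and by the definitions as written it leaves a patient MACE-free in the logistic and ROC analyses unless a non-fatal component was recorded first. Separately, the secondary death outcome is worded inconsistently between the Methods and Table 2, and stroke is placed differently in the abstract and the Methods.

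The gap follows from the text alone. Its size does not: about 0.4 to 3.4 of 150 patients, or 3% to 28% of roughly 12 expected MACE, rests on assumed values for the cardiac death rate and for the share that is non-sudden with no earlier component, and on the cited 8.1% applying to this study's MACE. The number of patients is small, but so is the number of events. The definitions should be settled before outcomes are analysed.

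**What to change.** - **Primary outcomes, Table 1 and Table 2:** replace sudden cardiac death with *cardiac death (sudden or non-sudden)*. Revisit the coronary-cause qualifier in Table 2 at the same time; otherwise a cardiac death from another cardiac cause could still fall between the two outcomes.
- **Secondary outcomes, Table 1 and Table 2:** use one wording for the exact complement, *non-cardiac death, including stroke death*.
- **Abstract and Methods:** state once whether stroke is part of MACE or a secondary outcome, and use that throughout.
- **Recurrent infarction:** adding it to MACE is optional. It would need a new definition in Table 2 and a new follow-up item in Table 1, so it is not free.

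The death changes need little or no new data collection, since deaths are already followed to 12 months; the rows in the two tables are reworded and each death is classified as cardiac or not. Because outcome indicators change, the section on modification of the protocol requires agreement of the research group, ethics approval and a report to the registry, among others. Patient management is unaffected.

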### Study protocol

#### Participants’ timeline

The procedure of participants’ enrollment and assessment timeline are presented in Fig. 1.

**Fig. 1 Fig1:**
[figure not shown]
Flowchart of the participants throughout the study. ACS: Acute coronary syndrome

#### Blood sample and data collection

Peripheral blood samples of these patients were obtained within 24 h of admission and collected in heparin anticoagulant tube (2–4 mL). Samples were placed at room temperature for testing within 24 h. Clinical data of patients such as age, gender, history of hypertension, coronary heart disease and diabetes mellitus, body mass index (BMI), white blood cell count, level of hemoglobin, platelet, creatinine, aspartate aminotransferase (AST), alanine aminotransferase (ALT), lipid profile, left ventricular ejection fraction, left ventricular end-diastolic volume etc. were collected. The results of coronary angiography were recorded as well.

#### Flow cytometry analysis

a. Cell surface stainingBlood is added to the tube, antibodies against the surface specific antigens of various subtypes of monocytes, macrophages, T cells, CD47, sirpα, Tim-3 and S100A4 were added and incubated for 30 min away from light.b. Erythrocyte lysingErythrocytes were lysed by lysing buffer at room temperature for 15 min until cell suspension was clear and transparent.c. Flow cytometry analysisThe stained cells were detected by flow cytometry. FlowJoV10.8.1 (BD research) was utilized to analyse the data.

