## Background

Coronary heart disease (CHD) is the leading cause of death and morbidity worldwide, causing serious economic burden to the society, among which acute coronary syndrome (ACS) is a type of CHD with the most acute onset and the highest mortality [1]. ACS includes ST-segment elevation myocardial infarction (STEMI), non ST-segment elevation myocardial infarction(non-STEMI) and unstable angina (UA). Although reperfusion therapies such as percutaneous coronary intervention(PCI) have been widely applied and improved early survival, major adverse cardiovascular events (MACE) after ACS such as in-stent restenosis, severe ventricular arrhythmia, heart failure, recurrent angina pectoris, and sudden cardiac death, still need to be concerned [2].

Numerous studies indicated that inflammatory response after ACS is a precisely regulated process and is a significant link in the instability and development of atherosclerotic plaques which acts as a pivotal role in clearing cellular debris and recovery after ACS [3–5]. Dysregulation of inflammation or prolonged inflammation may lead to adverse cardiac remodeling and MACE [6].

The innate immune response and acquired immune response are primary part of the inflammatory process of ACS. Mononuclear phagocyte system (MPS) participates in the former response, including macrophages, monocytes and dendritic cells [7]. In addition, imbalance of necrotic cell clearance can lead to enlarged myocardial infarction [8]. T cells, nature killer T cells(NKT cells) and tim-3 (also known as CD366 or T-cell immunoglobulin and mucin containing Protein-3), which is a sign of T cell exhaustion, participate in the latter response [9–11].

Calcium ion is an important second messenger of cells, the calcium metabolism engaged in the progression of various cardiovascular diseases. S100A4, a calcium ion binding protein, is a member of the S100 protein family [12]. This calcium ion binding protein family has been proved to be involved in various biological processes, for instance, cell apoptosis, Ca^2+^ homeostasis and above all, inflammation [13]. In our previous study, results indicated that the expression of S100A4 elevated in peripheral leukocyte of ACS patients.

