## Methods

### Aim of the study

To detect the characteristics of various subtypes of monocytes, macrophages, T cells and explore the expression of CD47, sirpα,S100A4 and Tim-3 on these cells in peripheral blood of ACS patients and investigate the relationship between them and the occurrence of MACE 1 year later.

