Our previous study found that expression of S100A4 elevated in peripheral leukocyte of ACS patients. S100A4 is a polypeptide protein, mainly composed of 101 amino acids, belonging to the S100 protein family, in which there are a total of 21 identified members, and it is also one of the largest subfamilies of calcium ion binding protein family [12]. Studies have shown that S100A4 protein can promote tumor invasion and metastasis, regulating a variety of cell functions. When combined with calcium ion, S100A4 protein is a crucial key to differentiation, proliferation of cells, muscle contraction, inflammatory and apoptosis through the pathway of calcium ion signal transduction [38–40]. A study has shown that the level of S100A4 will increase in ACS patients, which may become a new biomarker to predict ACS [41]. S100A4 knockout can aggravate ventricular remodeling, myocardial fibrosis, and distal myocardial capillary density reduction in mice [42]. Whether elevation of S100A4 affects the prognosis of ACS patients is unknown yet.

In this study, we assume that the characteristics of various subtypes of monocytes, macrophages, T cells and the expression of CD47, sirpα and S100A4 on these cells in peripheral blood differs in ACS patients and will affect the prognosis of these patients, so this protocol were set to detect the account and distribution of classical monocytes, non-classical monocytes, intermediate monocytes, M1 type macrophages, M2 type macrophages, CD4 positive T cells, CD8 positive cells and NKT cells and the level of CD47, sirpα, tim-3 and S100A4 by detecting different surface markers through flow cytometry. Then primary outcomes are observed during hospitalization and 3,6 and 12 months after discharge of participants. It is expected that this study will reveal the possible targets to improve the prognosis or prevent from occurrence of MACE. Since it’s a multicenter study, the enrollment rate of participants will be accelerated and it can ensure that the collected data are more symbolic and improve the richness and credibility of the test basis. We will use the SPIRIT checklist to improve the quality of the study.

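### S100A4 is measured only by a surface stain, so the result cannot answer the protocol's question about leukocyte S100A4 expression and MACE

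*Protocol article*

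**What the plan says.** The Flow cytometry analysis section of the protocol article gives a lettered procedure with three steps. Step a is headed as surface staining: "a. Cell surface stainingBlood is added to the tube, antibodies against the surface specific antigens of various subtypes of monocytes". The four marker antibodies go in during the same step: "CD47, sirpα, Tim-3 and S100A4 were added and incubated for 30 min away from light". Step b is erythrocyte lysis and step c is acquisition and analysis. No other staining step appears.

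The Discussion repeats the principle. It plans to obtain "the level of CD47, sirpα, tim-3 and S100A4 by detecting different surface markers through flow cytometry".

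The reasons for studying S100A4 are in the Background and the Discussion. The Background introduces calcium as a second messenger of cells and then says: "S100A4, a calcium ion binding protein, is a member of the S100 protein family". It gives a result from the group's own previous study as the motivation: "results indicated that the expression of S100A4 elevated in peripheral leukocyte of ACS patients". The Discussion says that S100A4 bound to calcium acts "through the pathway of calcium ion signal transduction", cites knockout evidence in mice, and calls its effect on the prognosis of ACS patients an open question.

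The Aim of the study section says the study will "explore the expression of CD47, sirpα,S100A4 and Tim-3 on these cells in peripheral blood of ACS patients" and relate these measurements to MACE one year later.

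**The concern.** A stain on intact cells shows only what an antibody can reach from outside. That suits a molecule on the membrane. S100A4 is introduced differently: it binds an intracellular messenger, works through calcium signalling, and is of interest because its expression in leukocytes was raised. The protocol neither calls it a surface molecule nor justifies measuring it as one.

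What is at stake is the interpretation of one of the four markers. Under the Statistical analysis section, indicators that are significant in simple comparisons go into a stepwise logistic model and then a ROC analysis. An S100A4 variable from a surface stain would pass through that sequence labelled as S100A4 expression. If it dropped out, the report would tend to say that S100A4 expression does not predict MACE, although cellular expression had not been measured. If it stayed in, a surface signal would be presented as evidence on expression and as a possible target.

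**Working it through.** The protocol states no figure on this point, so there is nothing to recompute. The check sets the procedure beside the rationale.

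1. **Where the antibody goes.** It is in step a, headed as surface staining, with CD47, SIRPα and Tim-3, in a single 30-minute incubation on whole blood (Flow cytometry analysis).

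2. **What follows.** There is a 15-minute red-cell lysis, then acquisition. Fixation, permeabilisation and a later intracellular stain are all absent. The lysing buffer's composition is not given. Even if it fixes or permeabilises cells to some degree, the antibody is added before it and the step is described as a surface stain, so an unstated side effect of the buffer cannot stand in for an intracellular measurement.

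3. **Is this only a detail lost in a short article?** No. The procedure positively assigns S100A4 to the surface step, and the Discussion independently says that its level comes from detecting surface markers. Two places state the same choice.

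4. **How the four molecules are described.**
   - SIRPα: the Discussion places it mainly on the surface of macrophages.
   - CD47: the Discussion describes it as the molecule on other cells that SIRPα binds.
   - Tim-3: the Background and Discussion describe it as a sign of T-cell exhaustion and give it a CD number.
   - S100A4: a calcium-binding protein acting through calcium signalling, with raised expression in leukocytes. No surface location is given.

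   Of the four, S100A4 is the one whose stated rationale is intracellular signalling.

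5. **What the readout can and cannot say.** Write cellular S100A4 as T = S + I, with S the part accessible at the surface and I the part inside the cell. The assay as described sees S, plus any non-specific signal. The protocol gives no relation between S and T. If I differs between patients with and without MACE while S does not, the result is null although T differs. If S differs because of surface binding alone, the result is positive although production by the cell may not differ. Neither result about S determines the result about T.

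6. **Scope.** S100A4 is 1 of 4 marker molecules in the aim. No sample size, power, error rate or event count depends on it.

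**The case against.** The strongest reply has three parts.

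First, the document never says in which compartment S100A4 lies. Calcium binding and a role in signalling suggest the cell interior but do not prove it. The aim is worded as expression *on* the cells, and a surface stain agrees with that wording. This stands in part. It rules out saying that the assay is invalid for any purpose: a surface-associated pool is a legitimate target if named and justified. It does not rescue the wider reading, because the rationale concerns expression in leukocytes and a signalling function, and the protocol does not tell the reader that only the surface pool is meant.

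Second, this is a condensed article, and bench detail belongs in a laboratory procedure that is not shown. That is right for isotype or fluorescence-minus-one controls, viability dye, antibody clones and gating; their absence is no finding. It does not dispose of the choice of compartment, which the article states twice.

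Third, only one of several exploratory markers is affected. That is correct and limits the weight of the point.

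A reader might also infer more than the documents allow:
- **That the signal is merely background or cell damage.** Samples may stand at room temperature with testing within 24 hours, so damaged cells are a possible contributor. Nothing in the protocol shows that they dominate.
- **That the results could not be compared with the group's previous study.** That study's assay is not described, so comparability is unestablished, not disproved.
- **That a quarter of a full grid of readouts is lost**, by crossing the cell subsets listed in the Discussion with the four molecules. The protocol defines no such grid, and it ties Tim-3 and SIRPα to particular cells.

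**Conclusion.** The concern holds in this form: S100A4 is assigned to a surface stain on unpermeabilised cells, while the rationale is about a calcium-signalling protein with raised leukocyte expression. As written, the readout supports statements about surface-accessible S100A4 only, and no conclusion in either direction about leukocyte S100A4 expression and MACE.

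The size is one of four marker molecules, on whichever subsets it is read. The primary outcome, the planned 150 patients, the follow-up and the other three markers are unaffected. The point should be settled before any S100A4 result is interpreted; it does not threaten the study as a whole.

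The conclusion rests on two assumptions. One is basic method: an antibody on intact, unpermeabilised cells does not measure protein inside them. The other is a reading of the rationale: that the S100A4 of interest is cellular expression, which the Background and Discussion suggest but do not state. If the investigators intend the surface pool, the remaining defect is one of labelling and of the scope of the claim.

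**What to change.** State which S100A4 pool is the target.

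- **If it is cellular expression:** in the Flow cytometry analysis section, remove S100A4 from the surface step and add a separate fixation/permeabilisation and intracellular stain on the same blood sample. In the Discussion, stop describing S100A4 as read through surface markers.
- **If it is the surface pool:** say so, give the reason, name the variable 'cell-surface S100A4' throughout, and limit the conclusion to it.
- **For samples already stained as described:** use the same restricted name and conclusion, and do not pool them with intracellular measurements. The abstract specifies fresh processing and no storage is described, so re-assay is probably not possible; an early decision matters for that reason.

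The cost is reagents, extra bench time per sample, and a check that the surface stains tolerate the added step. It needs no additional patients, visits or blood draws. Relabelling costs only wording.
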